# Rationale and design for Healthy Hearts in Manufacturing (HHM): A pragmatic single-arm hybrid effectiveness-implementation study for hypertension management and tobacco cessation

**DOI:** 10.1016/j.conctc.2025.101444

**Published:** 2025-02-03

**Keywords:** Quality improvement, Tobacco cessation, Hypertension, Worksite health centers

## Abstract

**Background:**

Heart disease is the leading cause of mortality in the United States and contributes more than $320 billion annually in health care costs and lost productivity. Manufacturing employment is associated with higher rates of hypertension and smoking. Many large manufacturers provide health services to employees and their family members through worksite health centers (WHCs). Several quality improvement interventions for hypertension and tobacco cessation have shown to be effective in community-based primary care sites. The Healthy Hearts in Manufacturing (HHM) study aims to implement and test these interventions in WHCs.

**Methods:**

Two organizations that operate WHCs at manufacturing sites volunteered to participate in the 58-month HHM research study. The HHM intervention involves monthly coaching to assist WHCs with implementing evidence-based strategies for hypertension management and tobacco cessation advocated by the Million Hearts initiative and the U.S. Preventive Services Task Force. A pragmatic, Type II hybrid effectiveness-implementation study design is used to evaluate HHM. The approach is inspired by the stepped-wedge cluster-randomized trial to assess intervention effectiveness. We will conduct interviews to identify facilitators and barriers to implementation and budget impact analysis to estimate the financial impact of the HMM interventions and the potential healthcare savings to companies and Medicare.

**Results:**

Twelve WHCs were randomly selected to enroll in HHM. The WHCs are in nine states and provide primary care services for employees and family members of four manufacturing companies. Baseline patient smoking rates ranged from 13 % to 59 % across WHCs. The percentage of patients with blood pressure of 140/90 or greater ranged from 7 % to 56 % across WHCs.

**Conclusion:**

This exploratory five-year research study will identify facilitators and barriers to implementing the HHM interventions in WHCs, evaluate the effectiveness of hypertension management and use of tobacco screening and cessation, and provide evidence of HHM's potential cost-effectiveness for employers and Medicare.

## Background

1

Heart disease is the leading cause of death in the United States (US) and contributes more than $320 billion annually in healthcare expenses and lost productivity [1,2]. Manufacturing communities, which are largely small and rural, have a significantly higher incidence of heart disease and its risk factors, such as smoking and obesity, compared to non-manufacturing communities [[3], [4], [5]]. Currently, there are 13 million manufacturing workers in the US; they are predominantly male and older than workers in other industries [6,7]. Jobs in manufacturing are also associated with higher rates of hypertension, physical inactivity, inadequate sleep, binge drinking, and fewer quality-adjusted life years [[8], [9], [10], [11], [12]].

Many large manufacturing companies, particularly those located in areas with limited primary care availability, provide health services for employees, spouses, dependents, and retirees through worksite health centers (WHCs) [13,14]. According to a recent national survey, 31 % of employers with over 5000 employees offer WHCs [15]. The WHCs usually have a limited staff that typically includes a nurse practitioner (68 %), physician (66 %), medical assistant (62 %), and/or nurse (53 %) [15]. Many WHCs are designed to function as primary care medical homes, emphasizing accessible care [15]. To encourage utilization of WHC services, many do not charge patients for care or charge only a nominal fee. Given their affordability and accessibility, WHCs are well-positioned to address chronic disease, poor health behaviors (e.g., smoking), and other health deficiencies prevalent in the US manufacturing communities.

Healthy Hearts in Manufacturing (HHM) is a 58-month (September 2023–December 2028) research study that seeks to provide coaching to 12 WHCs based at manufacturing sites to implement evidence-based quality improvement (QI) interventions related to hypertension management and tobacco cessation. HHM is testing the use of a coaching model as the strategy to support WHCs to implement best practices and improve their capacity for QI. The coaching includes health information technology support; data, feedback, and benchmarking; and expert consultation. These supports are delivered through practice facilitation, meaning a coach works with each participating WHC to help the WHCs make meaningful changes. HHM's approach to QI expands and builds upon successful elements of Healthy Hearts in the Heartland [16], Healthy Hearts in Michigan [17], and the Agency for Healthcare Research and Quality's EvidenceNOW initiative [18], which introduced coaching and the QI interventions in community-based primary care. HHM is an exploratory study to implement and test the coaching and QI interventions in WHCs for the first time. It is supported by a Large Research Demonstration and Dissemination (R18) grant from the Agency for Healthcare Research and Quality, which is designed to foster the application of existing knowledge.

HHM includes three components: (1) adapting the evidence-based hypertension management and tobacco cessation recommendations for use in WHCs, (2) evaluating the ability of WHCs to implement components of the HHM intervention by identifying facilitators and barriers to implementation and testing the effectiveness of the model to improve hypertension management and tobacco use screening and cessation, and (3) estimating the financial impact of HHM and its potential for health care savings to manufacturing companies and Medicare. This paper focuses on the second and third components. Here, we describe the inclusion, exclusion, and randomization of WHCs; the approach to identifying facilitators and barriers to implementation; and the analysis plan to examine our hypotheses and estimate the budget impact of HHM.

## Material and methods

2

### Study setting and participants

2.1

WHCs were recruited in advance of the study with assistance from the National Association of Worksite Health Centers, which hosted a webinar for members to learn about the study. WHCs were eligible if they provide primary care (i.e., not just occupational health or vaccines) and use an electronic health record (EHR) capable of extracting data needed for reporting outcome measures used in this study. Two organizations that operate WHCs volunteered to participate in HHM, and they are identified as Companies A and B in this paper to facilitate confidentiality. Company A is among the 50 largest private companies in the U.S. and operates WHCs for employees and dependents at its manufacturing sites. Company B is a health care organization that operates WHCs for multiple companies, including several manufacturers.

### HHM interventions

2.2

HHM interventions are evidence-based and focus on the clinical areas of hypertension management, tobacco screening and cessation, advocated by the Million Hearts initiative and the U.S. Preventive Services Task Force [19]. Specifically, HHM includes clinical interventions in four areas: improving accurate blood pressure measurement and treatment, identifying patients with hypertension and smokers through electronic health record (EHR) registries, self-monitoring of blood pressure (SMBP) programs, and an “Ask-Advise-Connect” approach to support tobacco cessation. Here, tobacco is defined as any tobacco-derived product for human consumption, including cigarettes, cigars, smokeless tobacco, and electronic nicotine delivery systems like vapes and e-cigarettes [20]. A list of QI strategies associated with the interventions is shown in Table 1.

**Table 1 tbl1:** Healthy hearts in manufacturing interventions, quality improvement (QI) strategies, and facilitation activity examples.

HHM Intervention	QI Strategies	Examples of Facilitation Activities
Improving accurate blood pressure (BP) measurement and treatment	• Training on accurate BP measurement (AMA guidelines) • Implement BP treatment protocol • Implement alerts or clinical decision supports for patients with uncontrolled BP • Encourage use of validated, automated BP cuffs for measurement	• Measurement of patient BP at least stressful times • Strategic placement of instructions for accurate BP measurement • Assessment of potential delivery of patient education by portal/SMS message • Training on BP on pharmacotherapy • Training on patient shared decision making/motivational interviewing • Redesign WHC workflow to facilitate accurate BP measurement • Assessment of WHC barriers to BP protocol adoption • Engagement of WHC leadership to obtain validated, automated BP cuffs • Identification and dissemination of WHC prescribed BP management (i.e., coverage, available on site, distribution during the workday)
Identify patients with hypertension and smokers through electronic health record (EHR) registries	• Generate a list of patients with uncontrolled BP • Generate a list of patients who smoke • Implement a protocol for outreach and follow up for patients with hypertension or who smoke	• Assessment of EHR documentation in structured data fields for tobacco use screening and BP measurement • Work with information technology/leadership/health center on data field documentation to capture data required for reports • Promote use of decision tools during visit and/or electronically • Assessment of workflows to facilitate follow up visits and document in EHR
Self-monitoring of blood pressure (SMBP) programs	• Design and implement workflows for patients to perform and report home BP measurements • Design and implement workflows for WHC clinicians to educate patients on SMBP	• Engagement of WHC leadership establish SMBP program (e.g., BP cuff loan program, funds for new home monitors)
An “Ask-Advise-Connect” approach to support tobacco cessation.	• Screen patients for tobacco use status • Document status in the EHR • Implement clinical alerts/decision support for patients who identify as smokers • Offer tobacco cessation interventions (i.e. counseling, pharmacotherapy, Quit line) and documenting in EHR • Document tobacco cessation interventions offered in the EHR • Redesign workflows to provide tobacco cessation counseling and/or prescribing • Implement referrals to state quit line; close the “referral loop”	• Assessment of “closure” of state quit line referral loop • Assessment of feasibility of electronic delivery of education (portal/SMS messages) • Training on pharmacotherapy for tobacco cessation • Training on patient shared decision tools/motivational interviewing • Training on counseling vs. advice for tobacco cessation • Identification of barriers to tobacco cessation protocol adoption • Identification and dissemination of WHC prescribed tobacco cessation medication options (i.e., coverage, available on site, distribution during the workday)
		**Facilitation Activities Related to All Four Clinical Interventions**
		• Assess availability/access to health center before/during/after shift • Assess wellness incentives/alignment with company goals • Work with leadership to promote incentive/raffle programs • Assess health center relationship with sponsoring company • Develop community resource list • Instruct on QI methodology

AMA = American Medical Association; BP = blood pressure; MAP = measure accurate blood pressure; EHR = electronic health record; QI = quality improvement.

The clinical interventions are reinforced through health information technology support, data, feedback, benchmarking, and expert consultation. These supports are delivered through practice facilitation, meaning each participating WHC receives personalized coaching to help the practices make meaningful changes. Practice facilitation is an evidence-based method to help primary care practices implement new approaches to improve the quality of care. It is associated with successful QI implementation and improvement in care delivery and chronic disease outcomes [[21], [22], [23], [24], [25], [26]]. One study found that practices are 2.8 times more likely to adopt evidence-based guidelines with practice facilitation [27]. Practice-facilitated strategies can improve care for those who regularly visit the clinic and also those who do not. For the HHM study, the practice facilitator is an experienced nurse with expertise in using health informatics to support QI. She has provided practice facilitation expertise on several EvidenceNOW projects that focus on similar clinical interventions for hypertension and tobacco cessation. Table 1 includes a list of activities that she will undertake associated with each HHM clinical intervention.

Fig. 1 shows the Implementation Research Logic Model for HHM [28]. The Logic Model outlines how the specific determinants (intervention characteristics, inner and outer setting, process, and individual characteristics) inform the HHM implementation strategy that drives the change mechanisms, with the goal of leading to improved outcomes.

**Fig. 1 fig1:**
[figure not shown]
Implementation Research Logic Model for Healthy Hearts in Manufacturing (HHM) Description: Implementation Research Logic Model for HHM, outlining how specific determinants, such as intervention and individual characteristics, inform the HHM implementation strategy that drives the change mechanism, with the goal of improved outcomes.

### Study design

2.3

The HHM study design is inspired by stepped-wedge, cluster-randomized trial but differs in key ways with its smaller sample size, exploratory nature, and pragmatic focus. It is best described as a pragmatic single-arm hybrid effectiveness-implementation study, emphasizing the implementation and testing of HHM in WHC's unique clinical setting and practical application [17]. Specifically, the intervention is administered and measured at the WHC level, and WHC-level aggregated data are retrieved from existing EHR registries. The first 10 months of the project are dedicated to logistic planning, interviews with WHC clinicians, and adaptation of HHM strategies. All WHCs begin in the baseline phase and then shift to the intervention phase at staggered time points. The baseline phase is the control condition, during which WHCs continue with their usual care for at least six months. The baseline phase begins in HHM's eleventh project month for all WHCs. The intervention phase, which lasts for 12 months, is when WHCs receive coaching on the HHM clinical interventions. Once the intervention phase is completed, each WHC will be moved to a maintenance phase, which lasts for at least six months. During such time, although WHCs will no longer receive any coaching, data collection will continue. Fig. 2 illustrates the study timeline for the participating WHCs. [NAME BLINDED FOR PEER REVIEW] Institutional Review Board (IRB) approved the HHM protocol and serves as the single IRB.

**Fig. 2 fig2:**
[figure not shown]
Healthy Hearts in Manufacturing (HHM) Study Timeline Description: The illustration of the study timeline for all participating worksite health centers inspired by the stepped-wedge cluster-randomized trial design.

### Randomization

2.4

We used stratified randomization based on WHCs' parent companies (i.e., Companies A and B) to ensure the balance of WHCs across treatment sequences. A total of 12 WHCs were selected, seven from Company A and five from Company B, determined by the companies’ capacity and willingness to participate. Within each company stratum, the timing of the implementation introduction was randomly allocated [29]. In an effort to minimize participation burdens on the Companies (i.e., company leaders participated in kick-off calls with the WHCs as they began the intervention), we alternated intervention start dates between WHCs from Companies A and B (starting with those with the smallest numbers) to balance rollout across the two companies over time. Company A was assigned to start first because it had more WHCs participating. All randomization was conducted in SAS (version 9.4, SAS Institute Inc, Cary, NC).

### Data collection

2.5

Data will be collected from multiple sources, including EHRs; tracking documents recorded by the practice facilitator using the Facilitation Activity and Intervention Tracing System (FACITS); and through interviews with company leaders, clinicians, and staff at the WHCs. Throughout the study, no individual or patient-level data will be collected; only aggregated data at the WHC level will be included in the study.

WHC-level patient demographic information will be collected twice from all participating WHCs: three months before a WHC enters its intervention phase and one month after it completes its intervention period. The data will include the mean, median, first and third quantiles of the patient's body mass index (BMI) and systolic and diastolic blood pressure. We will also collect the number of unique patients in each age group per gender and the percentage of patients by race and ethnicity.

The practice facilitator will use FACITS to document the encounters with the WHCs and progress in implementing the QI strategies associated with the clinical interventions (Table 1). The FACITS platform includes forms to support the tracking of activities during each encounter, including visit duration, mode (in-person vs. virtual), type(s) of facilitation interventions engaged in, topics covered, participating clinic staff, and free text notes. Examples of some of the facilitation activities to be tracked in FACITS are shown in the third column of Table 1. Additionally, the practice facilitator will document progress on the implementation of each QI activity, noting whether each activity was not implemented and not intending to implement, not implemented but intending to implement, partially implemented, implemented but not sustained, and fully implemented and sustained. The practice facilitator will document the progress of each WHC quarterly in FACITS.

### Identifying barriers and facilitators to sustainable maintenance of Healthy Hearts in manufacturing in worksite health clinics

2.6

Given the relatively small number of participating WHCs, we will pursue a qualitative approach to identify facilitators and barriers to sustainable implementation. Our data collection instruments will follow the logic model (Fig. 1) to explore the determinants and implementation strategies that facilitated or hindered sustainable implementation and, ultimately, changes in outcomes. We will assess barriers and facilitators at each of the twelve participating WHCs by conducting individual interviews with company leaders, WHC administrators and clinical staff. These interviews will be conducted toward the end of each WHC's intervention period. Interviews will be conducted via Zoom, professionally transcribed, and stored in Atlas.ti, a qualitative software program, for analysis [30]. To manage the data and assist in identifying patterns and themes, we will apply a combination of deductive codes based on the semi-structured interview protocol and inductive codes based on emergent concepts following an initial reading of the transcripts [31].

### Evaluating the impact of HHM on hypertension management and tobacco screening and cessation

2.7

HHM uses two outcome measures derived from Clinical Quality Measures (CQM) from the Centers for Medicare and Medicaid Services (CMS): CMS165v10 (controlling high blood pressure) and CMS138v11 (tobacco screening and cessation intervention) (Table 2). These measures represent the HHM intervention's impact at the WHC level. The measures will be treated as proportions, with the numerator being the number of patients that met the measurement criterion and the denominator being the number of eligible patients during the measurement period. To calculate these two measures, several data components will be collected monthly from each participating WHC throughout the study period from the baseline through the maintenance phase, a total of 35 months. For each monthly data collection, we will use a 12-month look-back period, meaning that each data point represents aggregate outcomes from the previous 12 months. In the end, one data point related to hypertension management and one data point related to tobacco cessation will be collected per WHC per month, both reflecting data from the preceding 12 months. The 12-month look-back period was selected to align with the definition of the outcome measures and was determined to be feasible given the natural limitations of the participating WHCs' electronic health records systems. EvidenceNow projects using coaching and similar QI interventions have previously documented challenges associated with using EHR data to enable the calculation of performance measures [[32], [33], [34]]. Descriptive statistics will be calculated for all measurements monthly across the study period, including means and standard deviations, and ranges, or counts and percentages, as appropriate.

**Table 2 tbl2:** Primary outcome measures and related data elements.

Measure	CMS165v10 [35]	CMS138v11 [20]
Measure Definition	Percent of patients, 18–85 years of age, who had a diagnosis of essential hypertension starting before and continuing into, or starting during the first 6 months of the measurement period, and whose most recent BP was adequately controlled (<140/90 mmHg) during the measurement period.	Percentage of patients aged 18 years and older who were screened for tobacco use one or more times during the measurement period AND who received tobacco cessation intervention during the measurement period if identified as a tobacco user.^a^
Data Elements Collected Monthly from Electronic Health Records	1.The number of adults (18–85) who: had at least one visit to the health center during the measurement period; AND had at least one blood pressure measure recorded during the measurement period	
	2. The number of adults in (1) who have ever been diagnosed with hypertension	4.The number of adults in (1) who were screened for tobacco use during the measurement period
	3. The number of adults in (2) whose most recent systolic blood pressure measurement is ≤ 139 AND diastolic blood pressure measurement is ≤ 89	5. Number of adults in (4) who were identified as a tobacco user
		6. Number of adults in (5) who received a tobacco cessation intervention (including counseling and/or pharmacotherapy) during the measurement period.
Denominator	(2) Adults with hypertension	(1) Initial Population – rate 1
Numerator	(3) Controlled hypertension	(4) Adults who screened for tobacco use – rate 1

a Three rates are reported for CMS138v11: (1) Percentage of patients aged 18 years and older who were screened for tobacco use one or more times during the measurement period, (2) Percentage of patients aged 18 years and older who were identified as a tobacco user during the measurement period who received tobacco cessation intervention during the measurement period or in the six months prior to the measurement period, and (3) Percentage of patients aged 18 years and older who were screened for tobacco use one or more times during the measurement period AND who received tobacco cessation intervention during the measurement period or in the six months prior to the measurement period if identified as a tobacco user.

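### Table 2's data elements do not implement the measure definitions printed beside them, so the before-after change in both primary outcomes can mix a change in care with a shift in the denominator

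*Protocol article*

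**What the plan says.** Section 2.7, Table 2 prints a definition for each measure and, below it, the data elements that the health centers supply each month over a 12-month look-back.

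- **Hypertension, definition:** patients aged 18-85 "who had a diagnosis of essential hypertension starting before and continuing into, or starting during the first 6 months of the measurement period", with the most recent BP in the period below 140/90.
- **Hypertension, collected:** the denominator is element (2): "The number of adults in (1) who have ever been diagnosed with hypertension". Element (1) is adults 18-85 with a visit "AND had at least one blood pressure measure recorded during the measurement period".
- **Tobacco screening, definition (rate 1 in the table footnote):** "Percentage of patients aged 18 years and older who were screened for tobacco use one or more times during the measurement period".
- **Tobacco screening, collected:** the denominator is "1) Initial Population – rate 1", that is, element (1) itself, with its age cap and BP condition.

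Section 2.7 calls the outcomes derived from the CMS measures. Section 2.7.1 then names the primary outcomes as CMS165v10 and CMS138v11, and section 2.7.2 gives planning baselines of 44% and 20% under those names. The main analysis (2.7.1) is a paired *t*-test on the proportions from two non-overlapping 12-month windows.

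One of the four intervention areas in section 2.2 is "improving accurate blood pressure measurement and treatment". Table 1 adds work on structured-field documentation of BP and tobacco screening, and a strategy to "Implement a protocol for outreach and follow up for patients with hypertension or who smoke".

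**The concern.** The elements depart from the definitions in three ways.

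1. A recorded BP is required for both measures. A diagnosed patient with no reading in the window stays in the printed hypertension denominator and cannot meet its numerator; the extract removes that patient. Tobacco screening is assessed only in patients who had a BP recorded.
2. The tobacco denominator stops at age 85; the definition has no upper limit.
3. The hypertension denominator is wider on diagnosis. The definition wants a diagnosis "starting before and continuing into, or starting during the first 6 months of the measurement period", whereas the extract also admits diagnoses from the last six months of the window and resolved cases.

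The BP condition and the pool of diagnosed patients are things that HHM's activities could change. If they do, the two windows describe differently selected patients. The number of adults with a visit but no BP is not a data element, and no patient-level data are held (section 2.5). The BP-recorded share therefore cannot be known at either time point or corrected for later. Both sensitivity analyses model the same proportions. The limitations in section 4 do not mention the denominators.

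**Working it through.** **The plan's own figure.** Section 2.7.2: 12 centers, difference 0.15, SD 0.16, two-sided alpha 0.05. The noncentral-*t* power has df = 11 and noncentrality (0.15/0.16) × √12 = 3.248, which gives 0.840. The stated 84% reproduces, with 0.16 read as the SD of the paired differences. Power is not in dispute; the calculation is a yardstick for what follows.

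**Shift from BP recording (hypertension).** The documents give no recording rates, so these inputs are assumptions: r0 and r1 are the shares of diagnosed patients with a BP recorded before and after. Control among those already recorded is held at p = 0.44, so care does not change. Control among the newly recorded is p_new = 0.20 to 0.60.

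- Table 2 rate after: [r0·p + (r1 − r0)·p_new] / r1
- Rate on the printed definition: r0·p before, r0·p + (r1 − r0)·p_new after

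| BP recorded | p_new | Table 2 rate | Printed definition |
|---|---|---|---|
| 95% → 98% | 0.20 | 44.0 → 43.3 (−0.7) | 41.8 → 42.4 (+0.6) |
| 95% → 98% | 0.60 | 44.0 → 44.5 (+0.5) | 41.8 → 43.6 (+1.8) |
| 80% → 95% | 0.20 | 44.0 → 40.2 (−3.8) | 35.2 → 38.2 (+3.0) |
| 80% → 95% | 0.60 | 44.0 → 46.5 (+2.5) | 35.2 → 44.2 (+9.0) |

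For example, (0.80 × 0.44 + 0.15 × 0.20)/0.95 = 0.382/0.95 = 0.402.

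**Tobacco screening.** Same formula with p = 0.20 and 0 to 50% of the newly recorded patients screened. Recording 80% → 95% gives 0.160/0.95 = 0.168 to 0.235/0.95 = 0.247, a shift of −3.2 to +4.7 points. Recording 95% → 98% gives −0.6 to +0.9.

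**Late-window diagnoses.** Assume a share f of the hypertension denominator at both time points, with 20% control among them. The change is [(1 − f)·0.59 + f·0.20] − [(1 − f)·0.44 + f·0.20] = (1 − f) × 0.15.

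- f = 0.10: 0.551 − 0.416 = 0.135, a loss of 1.5 points
- f = 0.20: 0.512 − 0.392 = 0.120, a loss of 3.0 points

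**Effect on the test.** With the SD at 0.16, a shift of −3 points on the planned 15 takes power from 84% to 66%; +3 takes it to 94%. A pure +3 shift with no change in care rejects 9% of the time instead of 5%.

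**The case against.** Several points on the other side stand.

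- **Movement is not shown.** Most BP items in Table 1 concern accuracy. The registry lists patients with uncontrolled BP, who already have a reading. No listed strategy is to diagnose new hypertension. Documentation and outreach make a shift possible, no more, and if nearly every patient already has a BP recorded it is under 1 point.
- **The departures are not all restrictions.** Taking a diagnosis at any time widens the denominator. HHM cannot move the age cap, which probably matters little because the centers mainly serve working-age people (section 4).
- **A larger dilution is tempting but not supported.** A reader might apply late-window diagnoses to the post-intervention value alone: 59% falls to 55.1% or 51.2%, and 4-8 of the 15 points seem lost. The any-time rule applies at baseline too, so that reading needs a baseline share of zero, for which the documents give no ground.
- **The printed definition has its own exposure.** It rises with BP capture alone: +3.0 to +9.0 points in the 80% → 95% case. Whether capture should count is a choice of estimand, which argues for reporting both versions. A visit condition, kept for feasibility, can also be moved by outreach.
- **Partial disclosure.** The measures are called derived, and the monthly counts of elements (1) and (2) can be tracked. But sections 2.7.1 and 2.7.2 drop the qualifier, and those counts do not give the BP-recorded share.
- **Missing BP.** Counting it as not controlled is a reading of the printed words, which do not state the rule outright.

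**Conclusion.** The mismatch between Table 2's definitions and its elements is certain on the text and affects both primary outcomes. That it biases the before-after comparison is possible, not established, and the sign could go either way, depending on whether newly counted patients do better or worse than those already counted. A reader might infer that HHM does move the denominators; the documents show only that it works on what determines them.

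In size, the BP condition could shift the hypertension rate by under 1 point to about 4 points over the assumed recording ranges, and late-window diagnoses could cost about 1.5-3 points at an equal 10-20% share with 20% control. Every recording share, late-diagnosis share and control rate here is an assumption. The top of these ranges is large enough to affect a 12-center test, and the data now planned could not reveal it. It should be corrected.

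**What to change.** 1. **Tobacco:** use adults 18+ with a visit as the screening denominator, without the BP condition, and take the screened count from the same population.
2. **Added monthly aggregate counts:** adults with a visit, and diagnosed hypertensive adults 18-85 with a visit whether or not a BP was recorded. Apply the diagnosis-date limit where the EHR can date the diagnosis, and re-run past months where feasible. Where dates are unavailable, at least drop the BP condition and state the remaining departure.
3. **Hypertension:** compute the measure on the denominator as defined, with patients lacking a recorded BP counted as not meeting the numerator. Report the present BP-recorded version and the BP-recorded share at both time points beside it, so that gains in capture can be told from gains in control.
4. **Labels:** if the present elements must stay, stop calling the results CMS165v10 and CMS138v11.

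The cost is one revised query per organization. Retrospective extraction may be limited: section 2.7 already notes EHR constraints, and nothing shows that either organization can date diagnoses. The hypertension measure as defined also rises with better BP capture, which is why item 3 asks for both versions.
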